## Abstract

**Introduction:** Borderline Personality Disorder (BPD) is a prevalent condition that is often under-treated. This is partly because very few psychotherapists offer treatment for this disabling disorder. Internet-based self-management interventions could contribute to reducing the treatment gap but—mainly due to safety concerns—these have never been tested for BPD in controlled trials.

**Methods:** Patients with BPD will be recruited primarily via the internet and randomized to two groups: care as usual (CAU) alone) or the self-management intervention *priovi*® in addition to CAU. At the end of the diagnostic interview, all participants will discuss an emergency plan. The main outcome measure is the clinician-rated symptom severity using the BPD Severity Index (BPDSI). Secondary outcome measures include a range of self-reported scales, an SCID-diagnosis of BPD and several safety parameters including serious adverse events (e.g., a life-threatening event, hospitalization or suicide attempt).

**Discussion:** This trial will evaluate the effectiveness of the self-management intervention, *priovi*, in reducing symptoms of BPD. It will also assess the safety of its use in this target population. If successful, this intervention would be the first comprehensive internet intervention for the treatment of BPD and complement the wide range of internet interventions effective in treating other mental disorders, particularly depression and anxiety disorders.

**Trial Registration:** NCT03418142 (clinicaltrials.gov) on January 23rd 2018.

**Trial status:** recruiting, currently *N* = 108 (July 2018).

## Introduction

Borderline Personality Disorder (BPD) is a common mental disorder characterized by a pervasive pattern of instability in interpersonal relationships, self-image and affect as well as marked display of impulsivity (1). The prevalence of BPD is about 2% with higher prevalence rates in women than in men (2, 3). In Germany, the annual treatment costs for BPD amount to about 15% of the total costs incurred for mental disorders (4). About 75% of these costs are due to inpatient treatment, which can be substantially reduced by effective treatment (5). Although a number of effective psychological treatments exist for BPD (6), only about one-in-four patients receive psychotherapy even in relatively well-developed health care systems (7). Reasons for this treatment gap include unavailability of trained psychotherapists. In one study involving over 150 psychotherapists, about one-in-five outrightly refused to treat patients with BPD “out of principle” (8).

Internet interventions are considered a viable option to help reduce the treatment gap in mental health (9). Broadly, these interventions can be divided into teletherapy interventions and self-management interventions (10). In *teletherapy interventions*, therapists communicate with their patients via the internet (e.g., e-mail or video chat). In *self-management interventions*, knowledge and techniques based on evidence-based psychotherapeutic methods are taught by an internet-based computer program instead of a therapist. Mostly based on the principles of cognitive behavioral therapy, these interventions can be accessed on internet-enabled desktop computers as well as mobile devices. Self-management interventions can be offered in *guided* or *unguided* form. Guidance often comprises electronic messages that are aimed at increasing adherence to the intervention.

In general, self-management interventions have a number of advantages. These include scalability and availability that is independent of the location and opening hours of a therapist. They may thus be an alternative for patients with mental illness who do not or cannot seek therapy either because a therapist is not available where they live (e.g., patients living in rural or remote areas) or because they are unable to find some free time during office hours of most therapists (e.g., patients who work and raise children) (11). In the treatment of BPD, self-management interventions can have the additional advantage of being available in times of crises when a therapist is not immediately available. Here, they can offer *in vivo* skills coaching (12) and thus facilitate the transfer or adoption of newly acquired skills in everyday life (13).

Disadvantages of self-management interventions include the fact that there are a number of interventions on the market that have never been rigorously tested in clinical trials (10). Also, while randomized trials have found no difference between face-to-face psychotherapy and guided self-management interventions in terms of dropout and effect sizes (14, 15), these outcomes have been found to be less favorable in purely unguided self-management interventions (16, 17). An additional disadvantage of self-management interventions is the fact that they can only react to acute crises in a very limited fashion (usually by referring to emergency psychiatric services). As will be discussed below, this limitation is of particular concern in the treatment of patients with BPD.

Internet interventions have been successfully tested in many randomized clinical trials (RCT) that have been summarized in numerous meta-analyses. These meta-analyses attest to the efficacy and effectiveness of these interventions in treating symptoms of depression (18) and anxiety disorders (19, 20). These interventions have also been used successfully in RCTs of patients with post-traumatic stress disorder (21), substance use disorder (22), and even schizophrenia (23). To our knowledge, there is no randomized trial of a self-management intervention in the treatment of BPD.

Self-management interventions for BPD have been tested in open-label pilot studies. However, in these studies, the interventions have been applied in a *blended format*, i.e., the intervention was used in addition to face-to-face psychotherapy. These interventions include the “DBT Coach” that can be used as an adjunct to Dialectic Behavioral Therapy (DBT) (12, 24) and “priovi®,” a program that is based on the principles of Schema Therapy (13). Offered in the traditional face-to-face format, both DBT and Schema Therapy have been shown to be effective in the treatment of BPD (25). The pilot studies on the aforementioned self-management interventions have concluded that they are well accepted by patients and can contribute to the reduction of symptoms of BPD. There is also an ongoing randomized study comparing an internet-delivered Dialectical Behavioral Therapy Skills Training (iDBT-ST) to a waitlist control condition in suicidal individuals engaging in heavy episodic drinking (26).

Experts in the treatment of BPD agree that self-management interventions should be used mainly in the blended format described above. Reasons for this preference include the opportunity for corrective experiences with respect to dealing with conflict and intense emotions in face-to-face psychotherapy. Another reason against using self-management interventions as a stand-alone therapy for BPD are safety concerns in a patient population that frequently engages in self-harm, suicide attempts, or other risky behaviors (13). On the other hand, a considerable proportion of individuals with untreated mental illness state that they prefer not to depend on a professional for the management of their disorder (11). Also, the aforementioned studies did not indicate possible harm that came from the use of self-management interventions in the treatment of BPD. A meta-analysis of studies with patients suffering from depressive symptoms found that compared with control conditions, harmful effects were less likely during the use of self-management interventions (27).

We have therefore decided to conduct the first randomized controlled trial of a self-management intervention based on Schema Therapy (priovi®) in the treatment of BPD. Given the characteristics of this patient population, particular emphasis has been placed on safety aspects during the design of this trial. This includes the discussion of a crisis plan with every participant of the trial and the careful assessment of negative effects and serious adverse events. We hypothesize that the use of this intervention in addition to care as usual (CAU) will be more effective than CAU alone in reducing symptoms of BPD over 1 year. We have chosen “care as usual” as the comparison condition because we consider it unethical to withhold treatment for 1 year in subjects suffering from a disorder that is as disabling and potentially dangerous as BPD. CAU was also chosen because it enhances the external validity of our findings by testing whether the intervention improves outcomes compared to the care usually received in the health care system (28). Additional analyses will concern the safety parameters and a broad range of secondary outcomes.

## Methods

In the following, we will describe the protocol for this trial entitled “REVISIT-BPD” (Research Evaluating the EffectiVeness of Adding an Internet-Based Self-Management Intervention to Usual Care in the Treatment of Borderline Personality Disorder). The trial is registered at ClinicalTrials.gov (NCT03418142). The description follows the SPIRIT guidelines (29) and the CONSORT guidelines for internet-based interventions (30).

### Trial design

This is a rater-blind, randomized (1:1), controlled, parallel group, superiority trial examining the effectiveness of an unguided internet-based self-management intervention in the treatment of BPD.

### Setting

The recruitment of study participants takes place via different channels. The most important recruitment channel is online (e.g., via Google ads and a dedicated Facebook page—https://www.facebook.com/priovistudie/). Internet users who enter certain search terms (e.g., borderline self-help, borderline study, priovi, etc.) on the Google search engine are shown a short ad that refers to the study homepage (https://priovi-studie.de/). Furthermore, the study will be advertised on patient platforms and via patient associations. In addition, we will recruit participants via health insurance companies; these will send out a letter about the study once to each insuree who is eligible to participate. Interested patients may also be referred to the study homepage via other means (e.g., a recommendation by their treating clinicians).

### Participants

Patients will be included in the study if they have a total score of at least 15 on the BPD Severity Index (BPDSI) (31, 32) and a diagnosis of BPD according to DSM-5 (at least five definite criteria) (1) as assessed by the structured clinical interview for DSM-IV (SCID) (33, 34). A BPDSI score of below 15 has empirically been shown to be the cutoff for recovery of BPD (31). Patients can also be included, if they only meet the criteria for a probable BPD diagnosis (three definite and at least two probable of the DSM-5 criteria), but only if they have already received a diagnosis of BPD by their treating clinician. All patients also have to be at least 18 years of age; provide informed consent; have an adequate command of the German language; consult a psychiatrist/psychotherapist before randomization for confirmation of their diagnosis; be willing and able to participate in the planned diagnostic assessments. They will be excluded from participating in the trial if they meet diagnostic criteria for any of the following diagnoses on the MINI diagnostic interview (35): psychotic disorder (patients will not be excluded if they experience only transient, stress-related paranoid ideation that is consistent with a diagnosis of BPD); primary diagnosis of substance use disorder; schizotypal disorder.

### Interventions

All participants are permitted to use any form of treatment, including psychotropic medication and psychotherapy. Following a pragmatic design approach, CAU is not influenced by the investigators (28). Participants in the control condition receive only CAU. In addition, they receive information regarding freely available self-help material on the internet, and they are offered access to the internet intervention after the last follow-up assessment.

Participants in the intervention group receive access to the unguided self-management intervention *priovi* in addition to CAU. They will be informed that priovi does not replace their ongoing psychotherapy but is merely an addition to it. The priovi intervention was developed and is owned by GAIA group, Hamburg, Germany. It is based on the principles of Schema Therapy. In Schema Therapy, problematic BPD behaviors and symptoms are connected with so-called schema modes, i.e., emotional states related to dysfunctional schemas such as mistrust/abuse or abandonment. Examples of typical schema modes in BPD patients include the *angry/impulsive child* mode (related to anger outbursts and impulsive behaviors) and the *detached protector* mode (related to problematic emotion-avoidance strategies such as dissociation). In Schema Therapy patients learn to identify their schema modes and to understand the biographical background of these modes. Further along, the treatment goals in Schema Therapy are also related to these modes and include helping the angry child mode find adequate ways to deal with anger or reassuring the detached protector mode so that patients can reduce their emotional avoidance and learn healthier strategies to deal with emotions and relationships.

Priovi is comprised of eight modules that are organized in simulated dialogues and can be accessed over a period of 1 year. These modules are divided in a psychoeducation phase (BPD symptoms, human needs, childhood abuse, and modes) and an intervention and exercise phase (these are tailored to the modes of the user and include cognitive techniques, imagery exercises, and affirmative audios). Each session is tailored to the current mood state of the user and thus addresses the frequent mood shifts associated with BPD. It is recommended to use the intervention twice a week for half an hour. Participants using the intervention on this regular basis can complete the full content in about 6 months, but it is recommended to use the intervention for the full year to continue with the exercises. A full description of the intervention can be found elsewhere (13).

The intervention will be unguided but participants who have not logged onto the intervention until the fifth day will receive a reminder that will once again explain the login procedure. Also, the intervention will send automated messages that are designed to motivate the user to engage with the intervention and the content covered in the intervention on a regular basis. Participants will also be able to contact a hotline to receive technical support. The hotline will refer to the treating psychiatrist / psychotherapist for management of acute crises.

### Sample size

The sample size calculation is based on the expected difference between the intervention and the control group in the severity of BPD (measured with the BPDSI) at the 12 months assessment. Based on an estimated effect size of Cohen's *d* = 0.40, a power of 0.80 and an alpha level of 0.05, 100 participants are required in each condition resulting in a target sample size of *N* = 200. The effect size estimate was based on a recent meta-analysis (6), where the between-group effect for add-on designs (in which both groups received CAU and one group received an additional BPD therapy) was *g* = 0.40.

### Procedure and assessments

After providing online informed consent, all prospective participants will be assessed via an online questionnaire and a telephone interview to establish if the inclusion criteria have been met. The assessment by online questionnaire and telephone interview will also be used to establish the baseline (T0). At the end of the telephone interview an individual crisis plan is discussed with all participants, i.e., whether they have contact information at hand of people they could contact in case of an acute crisis, e.g., acute suicidal ideation or impeding severe self-injury. Crisis contacts include both professionals (psychiatrists/psychotherapists) and friends. All participants will also be made aware of the nationwide emergency number−112.

Following the telephone interview, eligible participants will have to ask a psychiatrist or psychotherapist to confirm in writing (using a form supplied by the study staff) that they are suitable for participating in an RCT of a self-management intervention for BPD. After the receipt of this confirmation by a psychiatrist/psychotherapist, participants will then be randomized. They are contacted again after 3 months (T1), 6 months (T2), 9 months (T3), and 12 months (T4). All assessments include an online questionnaire and a telephone interview except for the T3 assessment that only comprises an online assessment. All assessments and the respective measures to be used can be found in Table 1.

**Table 1 T1:** Schematic diagram of study timeline.

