### Outcome measures

All outcome measures are used in their German version. The main outcome measure is the Borderline Personality Disorder Severity Index (BPDSI) (31, 32), a clinician-rated semi-structured interview that is based on the DSM-IV criteria for BPD. It assesses the frequency of BPD-manifestations during the past 3 months. It has excellent psychometric properties: Cronbach's α = 0.85 in patients with BPD and interrater reliability of 0.98. It also has excellent criterion-validity and change sensitivity. All raters will have a bachelor or master degree in psychology, have experience in psychological diagnostic assessments and will have participated in a rater training. Before they are permitted to rate trial participants, raters will have to demonstrate adequate interrater reliability on an audiotaped interview. For each rater, we will also assess the interrater reliability of their third interview.

Secondary study outcomes and safety parameters that will also be assessed during the diagnostic interview include the presence of a diagnosis of BPD on the structured clinical interview for DSM-IV (SCID) (33, 34) and the presence of adverse or serious adverse events. The assessment of adverse events follows recommendations established in pharmacological research (36). Using a semi-structured interview, participants are asked whether they have experienced any of the following events during the observation period (past 33 months for baseline and since last assessment for all other assessments): life-threatening events (e.g., self-injury, drug intoxication, accidents, etc.), medical occurrences that require hospitalization and suicide attempts.

The following secondary outcomes and safety parameters are then assessed using self-report: severity of BPD using the BPD-Checklist (37), depressive symptoms using the 9-item Patient Health Questionnaire (PHQ-9) (38), symptoms of anxiety using a 7-item anxiety scale (GAD-7) (39), quality of life (QoL) using the five-dimension three-level version of the questionnaire developed by the EuroQoL group (EQ-5D-3L) (40) and negative effects of the intervention using the Negative Effects Questionnaire (NEQ) (41). Participants are also asked about the parallel use of psychotherapy.

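### The first follow-up adverse-event window (T1) opens at the T0 interview, before randomisation, so as written pre-allocation events enter the between-arm safety comparison behind the early-termination rule

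*Protocol article*

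**What the plan says.** All references are to the protocol article.

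- **Procedure and assessments, on T0.** The screening questionnaire and telephone interview also serve as baseline: "The assessment by online questionnaire and telephone interview will also be used to establish the baseline (T0".
- **Procedure and assessments, on what follows T0.** After the interview, an eligible participant asks a psychiatrist or psychotherapist to complete a form supplied by the study. Allocation and follow-up come next: "After the receipt of this confirmation by a psychiatrist/psychotherapist, participants will then be randomized. They are contacted again after 3 months (T1". The later contacts are at 6, 9 and 12 months.
- **Outcome measures.** Life-threatening events, hospitalisations and suicide attempts are asked about in a semi-structured interview. Baseline has its own look-back period. Every later interview looks back to the assessment before it.
- **Table 1.** Adverse events are collected at T0, T1, T2 and T4. T1 stands under the post-allocation heading. The clinician's confirmation stands in the T0 column, so the interval between T0 and allocation is not visible in the table.
- **Data management.** The steering committee compares serious adverse event frequencies between arms at internal audits. It ends the trial early if the intervention arm has significantly more. There is no independent monitoring committee.

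**The concern.** For T1, the preceding assessment is T0, and T0 lies before allocation. Read literally, the T1 interview collects serious events from a period in which nobody had an arm and nobody had access to priovi, and places them in a post-allocation column.

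Such events are expected equally often in both arms. Adding them leaves the expected difference in counts unchanged, but it shrinks the ratio and increases the variance of the counts. A real excess in the intervention arm is then less likely to reach significance. This matters more here than in most trials: the between-arm comparison is the stated trigger for early termination, it is made internally, and the article names safety as a main reason why such interventions had not been tested in controlled trials for this disorder.

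**Working it through.** **1. Order of events.** T0 interview, then written confirmation, then randomisation, then T1. The T1 look-back ends at T0. Let g be the months from T0 to randomisation. For any g above zero the T1 window includes g months before allocation. This follows from the stated text whether T1 is timed from T0 or from randomisation. The sentence order in Procedure and assessments favours randomisation, and that reading is used below.

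**2. Inputs.**
- From the article: T1 at 3 months, last interview at 12 months, look-back to the previous assessment.
- Assumed, because the article gives neither: g = 1, 2 or 3 months, and a true post-randomisation rate ratio R = 2.0 (intervention to control).
- Also assumed: a constant background event rate, equal in both arms before randomisation.

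**3. Formulas.** For follow-up of m months after randomisation:
- pre-allocation share of the window = g / (g + m)
- ratio seen = (g + m × R) / (g + m)

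**4. Results.**

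| g (months) | Share, T1 window (m = 3) | Ratio seen, T1 | Share, 12 months (m = 12) | Ratio seen, 12 months |
|---|---|---|---|---|
| 1 | 1/4 = 25% | 7/4 = 1.75 | 1/13 = 8% | 25/13 = 1.92 |
| 2 | 2/5 = 40% | 8/5 = 1.60 | 2/14 = 14% | 26/14 = 1.86 |
| 3 | 3/6 = 50% | 9/6 = 1.50 | 3/15 = 20% | 27/15 = 1.80 |

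With a delay of only half a month the ratios are 6.5/3.5 = 1.86 at T1 and 24.5/12.5 = 1.96 over 12 months.

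**5. Does the delay threaten the primary comparison?** The plan's own figure is reproduced first. The Sample size section states "Based on an estimated effect size of Cohen's *d* = 0.40", with "a power of 0.80 and an alpha level of 0.05, 100 participants are required in each condition". Two-sided, n per arm = 2 × (1.960 + 0.842)² / 0.40² = 98.1, or 99 rounded up. The t-test solution is 99.08, which rounds up to 100. Power at 100 per arm is 0.807 (normal) or 0.804 (t). This calculation takes no credit for baseline adjustment. Adjustment multiplies the standard deviation by √(1 − r²), where r is the assumed correlation between baseline and outcome. Power at 100 per arm is then 0.94 for r = 0.6, 0.87 for r = 0.4, 0.82 for r = 0.2 and 0.81 for r = 0. An older baseline could cost precision, but it would not by itself take power below the planned 0.80.

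**The case against.** **The look-back is an interview rule, not a counting rule.** The analysis plan, which is not shown, may set randomisation as the origin. The article plans Kaplan–Meier and Cox analyses for dichotomous outcomes. If these cover serious events, they need event dates, and gap events could then be separated. This is fair as far as the final analysis goes. It does not settle the audit comparison, which the article describes as one of frequencies. Nothing in the text removes the gap from the T1 window.

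**The T1 figures show the worst window.** This stands. The audits are not said to compare T1 data alone, and over the full year the dilution is mild. Early audits, when most follow-up is T1 data, would lie nearer the larger figures. Both the delay and the rate ratio are assumed.

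**The delay may be short.** This also stands as a limit on size. A clinician only has to complete a form, and the article presumes that many participants already have one. The Introduction does say "Reasons for this treatment gap include unavailability of trained psychotherapists", but that concerns access to treatment, not to a signature.

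**A stronger reading is tempting.** A reader might infer that randomisation can wait indefinitely, so that the baseline BPDSI goes stale. The BPDSI looks back over a limited period ("It assesses the frequency of BPD-manifestations during the past 3 months"), and the article itself notes: "A BPDSI score of below 15 has empirically been shown to be the cutoff for recovery of BPD". A late-randomised patient could thus already have fallen below the entry score. The document does not support making this a finding. The article states no maximum interval, but a screening window is the kind of detail that a condensed article leaves to the full protocol. The delay precedes allocation, so it is balanced between arms in expectation and cannot bias the group contrast. Planned power is kept, as step 5 of the working shows.

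**Conclusion.** The point holds for the adverse-event window only. That the T1 look-back opens before allocation follows from what the article states and needs no assumption beyond a delay above zero. The direction is also clear: the serious adverse event ratio is pulled towards no difference, which makes a real harm harder to detect under the termination rule.

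The size is illustrative. Under the assumptions listed in the working, the loss is material in the T1 window and modest over the year. It shrinks as the delay shortens, and the article reports no delay.

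The missing maximum interval between T0 and randomisation, and any ageing of the baseline score, are not part of the finding. Neither the primary efficacy comparison nor the sample size is called into question.

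**What to change.** - At T1, ask about adverse and serious adverse events since the participant's randomisation date, and record the date of each event. Later interviews can keep the look-back to the previous assessment.
- Use randomisation as the time origin for the audit comparison and for any time-to-event analysis of these events.
- Report events between T0 and randomisation separately as pre-allocation, outside the between-arm comparison.
- For participants already randomised (the article gives N = 108 in July 2018, against a "target sample size of *N* = 200"), reassign gap events where event dates were recorded, and state how many events could not be placed.

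The cost is a one-line change to the T1 interview and minor extra date recording. Eligibility, the baseline measurement and the visit schedule stay as they are.
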